### Sample size {14}

The sample size was calculated (nQuery 8 software, version 8.6.1.0, Statistical Solutions Ltd, Cork, Ireland) based on the primary endpoint of the study. Assuming SSI rates of 4% and 16% for the experimental and the standard group respectively (OR=4.571), the one-sided z-test (Group Sequential test of two proportions) at the 2.5% significance level with a total of two looks at the data will have overall 80% power to show superiority of the experimental over the standard arm if the study includes at least 232 patients (116 patients per intervention group). The calculation is continuity corrected due to the expected low proportion in the experimental group. The results assume that the group sequential design has one interim sequential test for monitoring and sample size re-estimation (two total looks at the data including final analysis), which means that an interim analysis is planned after half of the patients have reached 30 days post-surgery. The O’Brien-Fleming spending function is used to determine the efficacy test boundary and the non-binding futility boundary. The group sequential test boundaries (Z scale) for the interim and the final analysis are as follows:

Upper efficacy bounds: 2.963 and 1.969

Futility bounds: 0.555 (non-binding) and 1.1969.

A drop-out rate of about 20% is expected in this study, based on experience from similar trials previously conducted within the CHIR-*Net* trial network. Therefore, a total of 290 patients (145 per intervention group) should be included in the study.

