## Statistical methods

### Statistical methods for primary and secondary outcomes {20a}

The intention-to-treat (ITT) set consists of all patients who received irrigation of the abdominal cavity before closure of the abdominal fascia with one of the study solutions. Analysis will be performed as randomized regardless of the actual intervention and regardless of any further medical or surgical treatments. The Per-Protocol (PP) set consists of patients treated according to protocol, excluding any major protocol violations. The PP set will be analysed as treated. The Safety (SA) set will consist of all patients in the ITT set, analysed as treated.

All primary and secondary analyses will be performed on the ITT set. Sensitivity analysis of the primary endpoint will be performed on the PP set. The SA set will be used for the safety analyses. The incidence of SSI within 30 days after surgery will be compared between the two study groups using the one-sided group sequential test of two proportions at the 2.5% significance level with a total of two looks at the data. The primary endpoint analysis will be performed on the ITT set. Since the ITT set includes all patients who were treated in the study regardless of any further medical or surgical treatments, it is expected, that the SSI rates 30 days post-surgery will be available for most patients. Nevertheless, it is possible that some patients do not reach the primary endpoint due to death, withdrawal of informed consent, loss to follow-up, or other unforeseen reasons. Patients who die before day 30 will be considered as having SSI at time of death regardless of the intervention group, unless SSI was documented earlier. All other missing primary endpoint data will be dealt with using multiple imputations based on binary logistic regression models including LOC, ASA, BMI, age, diabetes, type of surgery, duration of surgery, use of wound-edge protectors, and intraoperative changing of gloves.

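### The named sensitivity analysis, on the per-protocol set, does not vary the missing-at-random assumption behind the imputation of up to 20% of primary outcomes

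*Protocol article*

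**What the plan says.** All in the protocol article:

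- **Statistical methods for primary and secondary outcomes {20a}.** The primary test is a "one-sided group sequential test of two proportions at the 2.5% significance level with a total of two looks at the data", on the ITT set. Deaths before day 30 count as SSI. For the rest, "All other missing primary endpoint data will be dealt with using multiple imputations", using logistic models whose listed covariates are all baseline or operative; study arm is not among them. Outcomes are expected to be available for most patients. On robustness the section says: "Sensitivity analysis of the primary endpoint will be performed on the PP set". The per-protocol set is defined by adherence to the protocol and is analysed as treated.
- **Methods for additional analyses {20b}.** Supportive logistic models are run on the ITT set with multiple imputation and on the per-protocol set.
- **Protocol non-adherence and missing data {20c}.** This repeats multiple imputation for the primary endpoint and adds no other method for it.
- **Sample size {14}.** "A drop-out rate of about 20% is expected in this study", which raises 232 patients to 290.

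**The concern.** A sensitivity analysis should vary the assumption most likely to affect the conclusion. Here the imputation assumes that a patient with unknown SSI status has the same risk as a followed patient with the same covariates. Removing protocol violators leaves that assumption as it was. The supportive models either reuse it or drop the same patients.

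The assumption could fail. None of the listed covariates is postoperative, so the model cannot use what happened to a patient after surgery. The surgical team knows the allocation ({17a}), and some exclusions follow from decisions taken during or after surgery (Visit 2). If those patients' outcomes are not kept, the loss could be related to infection.

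As planned, a significant result would be reported without showing how far the assumption can fail before the conclusion changes.

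**Working it through.** **1. The plan's own figures.** Inputs from Sample size {14}: "Assuming SSI rates of 4% and 16% for the experimental and the standard group respectively (OR=4.571"; 80% power; "Upper efficacy bounds: 2.963 and 1.969"; interim futility bound 0.555; "The calculation is continuity corrected due to the expected low proportion in the experimental group".

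- The two efficacy bounds give a one-sided error of 0.02498 at information 0.5 and 1. With the futility bound followed, 80% power needs a drift of 2.878.
- Per arm: 2.878² × (0.04 × 0.96 + 0.16 × 0.84) / 0.12² = 8.285 × 0.1728 / 0.0144 = 99.4.
- The Fleiss continuity correction gives (99.4/4) × [1 + √(1 + 4/(99.4 × 0.12))]² = 115.5, so 116 per arm and 232 in total.
- Drop-out: 232 / 0.80 = 290, or 145 per arm.

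Both figures reproduce. The allowance is 290 − 232 = 58 patients, 29 per arm. Against this stand 116 × (0.04 + 0.16) ≈ 23 expected observed SSIs and a planned difference of 116 × 0.12 ≈ 14 events.

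**2. Tipping point if the whole allowance is imputed.** Assumptions, none of them fixed by the protocol: 116 observed and 29 missing per arm, imputation by arm, missing controls at the observed 16%, many imputations, final look only. Let p be the observed experimental rate and q the rate among missing experimental patients.

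- Completed experimental rate: e = 0.8p + 0.2q.
- Rubin variance, experimental arm: e(1 − e)/145 + 0.2² × q(1 − q)(1/116 + 1/29).
- Control arm: 0.16 × 0.84/116 = 0.001159.
- z = (0.16 − e)/√(sum of variances), compared with 1.969.

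For p = 4%:

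- q = 4% (missing at random): difference 0.120, SE 0.0386, z = 3.11.
- q = 16% (the control rate): e = 0.064, difference 0.096, SE 0.0425, z = 2.26.
- q = 20.9%: e = 0.0738, difference 0.0862, SE 0.0438, z = 1.97. This is the tipping point, about 6 of 29.

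| Observed rates | z under missing at random | Tipping rate q | Infections among 29 |
|---|---|---|---|
| 4% v 16% | 3.11 | about 19–21% | about 6 |
| 6% v 16% | 2.47 | about 13–14% | about 4 |
| 7% v 16% | 2.17 | about 10% | about 3 |

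The upper end of each range uses the variance above. The lower end carries the uncertainty of the observed rate through the log-odds shift, replacing q(1 − q)/116 by [q(1 − q)]²/[116 p(1 − p)]. The 6% and 7% rows are illustrations of a smaller effect; the protocol does not give those rates.

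**3. Dependence on the share imputed (4% v 16%, variance as in step 2).**

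| Share imputed | Missing per arm | Tipping rate q |
|---|---|---|
| 5% | 7.25 | about 90% |
| 10% | 14.5 | about 42% |
| 15% | 21.75 | about 28% |
| 20% | 29 | about 21% |

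**4. False-positive illustration.** Suppose the true SSI rate is 16% in both arms, 20% are missing, and missing experimental patients have rate q. Observed experimental patients then have (0.16 − 0.2q)/0.8: 16%, 14% and 12% for q = 16%, 24% and 32%. Simulated one-sided rejection at the final look, with imputation by arm, is about 2.4%, 6.4% and 14%.

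**5. If study arm is left out of the imputation model.** With 4% v 16% observed, missing patients in both arms are filled in at about 10%. The completed rates are 0.8 × 4% + 0.2 × 10% = 5.2% and 0.8 × 16% + 0.2 × 10% = 14.8%. The difference is 9.6 points and z is about 2.5 instead of 3.1. Such a model pulls the arms together, so a positive result depends less on the assumption.

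**The case against.** The strongest reply is that the plan contains no misstatement. A per-protocol analysis is a conventional check against protocol violations, the text never says that it is meant to test the imputation, and a missing-not-at-random analysis is often left to an SAP. Part of this stands: an SAP that is not shown may contain one. But the article is not silent on the matter. It names the sensitivity analysis of the primary endpoint and describes the imputation model in detail, and what it names does not address the imputation.

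A reader might also infer that 20% of outcomes are expected to be imputed. The documents do not support that. The 20% is a drop-out allowance and so a ceiling. Deaths are scored as SSI, excluded patients can be replaced ({11b}), an SSI recorded at day 5 or 10 already counts, and {18b} provides visit windows, a form for the treating physician and a telephone fallback.

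A reader might further infer that follow-up will differ by arm. No section shows this. The intervention is given once, and patients and outcome assessors are blinded. Differential loss is possible, not documented.

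Finally, a positive result need not be fragile. At the planned effect it survives even when missing experimental patients have the control rate (z = 2.26). If the imputation model omits arm, as the listed covariates read, it leans on the assumption less still.

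**Conclusion.** The point holds in a limited form. The analysis named as sensitivity for the primary endpoint does not vary the missing-at-random assumption, and neither do the supportive analyses, although they are further analyses of the same endpoint.

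The size depends on the share imputed. At the 20% ceiling about 6 infections among 29 missing experimental patients overturn the planned effect. At 6–7% v 16% only 3 or 4 do, a rate below that of the control arm. At 5% imputed the planned effect is almost impossible to overturn. These figures assume imputation by arm, Rubin variance, missing controls at 16% and the final bound of 1.969.

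The documents do not support the claim that a positive result will probably rest on this assumption; they support only that the plan as stated would not show whether it does. This is a cheap improvement, not a defect in the primary test or the sample size.

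**What to change.** In Statistical methods {20a}, keep the per-protocol analysis as supportive. Name a delta-adjusted (tipping-point) multiple-imputation analysis on the ITT set as the sensitivity analysis for missing primary outcomes. Vary the SSI odds of missing patients separately in each arm, and report where the result crosses the final bound. Fix this before unblinding, and state at the same point whether the imputation model contains study arm.

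The cost is a sentence or two in the text and a loop around imputation code that is needed anyway. The sample size does not change. The downside is a little more analysis and possibly a less favourable range beside the primary result.

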## Assignment of interventions: allocation

### Sequence generation {16a}

The randomization list will be generated by an online randomization tool (Randomizer, Institute for Medical Informatics, Statistics and Documentation, Medical University of Graz, Austria; URL: http://www.randomizer.at). Online-Randomization will be performed at the end of the surgical procedure before the abdominal fascia is closed and will be stratified by LOC of the surgical procedure (LOC II–IV; Table 2). To assure balanced group sizes during the accrual, a block-wise randomization is applied.

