### Methods for additional analyses (e.g. subgroup analyses) {20b}

Since randomization will be stratified by LOC, supportive analysis of the primary endpoint will be performed using a binary logistic regression model with dependent variable SSI and covariates intervention group and LOC. In addition, the following parameters might influence the outcome, which is why they will be included as model covariates in an additional model:Operation-related risk factors: (a) type of surgery; (b) duration of surgery; (c) NNIS Risk Score, (d) use of wound-edge protectors; (e) intraoperative changing of gloves before skin closure; (f) presence of an enterostomy; (g) administration and timing of antibiotic prophylaxis;Patient-related risk factors: (g) BMI; (h) ASA score; (i) Age; (j) diabetes; (k) smoking; (l) alcohol abuse; (m) Charlson Comorbidity Index, (n) history of SSI; (o) history of radiotherapy; (p) history of chemotherapy, (q) days of hospitalization prior to surgery.

Supportive analysis of the primary endpoint will be performed on the ITT set using multiple imputations for any missing SSI values and on the PP set. Secondary endpoints will be analysed by intervention arm on the ITT set, using appropriate descriptive statistics. Any explorative statistical testing will be performed using a significance level of 5%. The assessment of safety will be based on the frequency of AE/SAE as defined in the protocol within the safety population consisting of all patients randomized into the study.

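### The primary test leaves out the LOC strata used for randomisation, so it is valid but conservative; the supportive additional model has too many covariates for the SSIs expected

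*Protocol article*

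**What the plan says.** - **Randomisation.** Under Sequence generation {16a}, allocation is done in blocks and "will be stratified by LOC of the surgical procedure (LOC II–IV; Table 2"). It takes place at the end of the operation, before the fascia is closed.
- **Prognostic weight of LOC.** Table 2 gives SSI rates of 3–11% (LOC II), 10–17% (LOC III) and above 27% (LOC IV).
- **Primary test.** Under Statistical methods {20a}, SSI incidence is "compared between the two study groups using the one-sided group sequential test of two proportions", with two looks. No stratification is mentioned.
- **Sample size {14}.** The same test is used for planning: "Assuming SSI rates of 4% and 16% for the experimental and the standard group respectively", a "one-sided z-test (Group Sequential test of two proportions) at the 2.5% significance level" that "will have overall 80% power" with "at least 232 patients (116 patients per intervention group").
- **Supportive model.** Methods for additional analyses {20b} states: "Since randomization will be stratified by LOC, supportive analysis of the primary endpoint will be performed using a binary logistic regression model" with arm and LOC as covariates.
- **Additional model.** The same section then lists parameters that may influence the outcome, "which is why they will be included as model covariates in an additional model". There are 18: seven operation-related and eleven patient-related (the letter g is used twice). No selection or penalisation is stated.

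**The concern.** When allocation is balanced within strata that predict the outcome, the arm difference varies less than the pooled two-proportion variance assumes. A pooled z test therefore rejects too rarely under the null and gives up some power. The protocol itself cites the stratification as the reason for adjusting for LOC, but applies that reason only to a supportive analysis.

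The additional model has the opposite problem. It carries nearly as many parameters as there are expected events. With ordinary maximum likelihood this pushes the treatment odds ratio away from 1 and, with sparse categories, can leave it without a finite estimate.

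**Working it through.** **1. The plan's sample size reproduces.** Unpooled variance: 0.04×0.96 + 0.16×0.84 = 0.1728. Fixed-design n per arm = 0.1728 × (1.960 + 0.842)² / 0.12² = 94.2. The continuity correction, (n/4)(1 + √(1 + 4/(0.12n)))², gives 110.2. The O'Brien-Fleming efficacy and futility spending inflates this by 1.056, to 116.4 (115.5 if inflated before correcting), against 116 stated. Then 232/0.80 = 290. The efficacy bounds 2.963 and 1.969 also reproduce. So N was computed for the unstratified test, with no credit taken for stratification.

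**2. Why the pooled test is conservative.** The pooled test uses p(1−p), with p the overall rate. With balanced strata, the variance that applies is Σ w·p_s(1−p_s), where w is the LOC share and p_s the LOC-specific rate. Let R be the second divided by the first. The effective critical value is then 1.969/√R. The LOC mix is an assumption in every example; each gives about 16% overall and stays within Table 2.

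- Mix 65/10/25 (LOC II/III/IV) at 5/15/45%: overall 3.25 + 1.5 + 11.25 = 16.0%. Pooled 0.1344; within-stratum 0.0309 + 0.0128 + 0.0619 = 0.1055; R = 0.785. Critical value 1.969/0.886 = 2.22, so the error is about 1.3%.
- Mix 50/20/30 at 7/13.5/33%: overall 16.1%. Pooled 0.1351; within-stratum 0.1222; R = 0.905. Critical value 2.07, error about 1.9%.
- Mix 60/25/15 at 11/17/34%: overall 15.95%. Pooled 0.1341; within-stratum 0.1277; R = 0.952. Critical value 2.02, error about 2.2%.

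**3. Simulation.** 116 per arm, common odds ratio across LOC, critical value 1.969, pooled z against Cochran-Mantel-Haenszel (CMH). Null error uses the control rates in both arms; power uses 4% versus 16% overall.

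| LOC mix II/III/IV | Control SSI % by LOC | Error, pooled / CMH | Power, pooled / CMH |
|---|---|---|---|
| 60/25/15 | 11/17/34 | 2.2% / 2.4% | 89.4% / 89.9% |
| 40/30/30 | 7.5/14.4/28.9 | 2.2% / 2.5% | 89.1% / 89.9% |
| 50/20/30 | 7/13.5/33 | 2.0% / 2.4% | 90.0% / 91.0% |
| 40/30/30 | 3.3/10.9/38.1 | 1.7% / 2.5% | 90.2% / 91.9% |
| 65/10/25 | 5/15/45 | 1.4% / 2.4% | 90.7% / 92.9% |

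Over all plausible mixes tried, the error is about 1.3–2.3% and the gain about 0.4–2.3 points. If the experimental rate is 6% (an assumption), the two 40/30/30 mixes go from 70.9% to 72.2% and from 71.4% to 75.2%; the overall range of gain is about 1–6 points. A steeper case with a LOC IV control rate near 59% gave 3.0 points at 4% and 7.3 at 6%; it is left out of these ranges as extreme. Adding the interim bound of 2.963 changed no error or power figure by more than about 0.1 point.

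**4. Additional model.** Expected SSIs: 116 × 0.16 + 116 × 0.04 = 18.6 + 4.6 = 23.2, or 145 × 0.20 = 29 if all 290 patients contribute. Parameters, taking one per listed covariate: 18 + 1 (arm) + 2 (LOC) = 21. Events per parameter: 23.2/21 = 1.1 and 29/21 = 1.4. Visit 2 lists eight surgery types that can be combined. Entered as eight indicators, they make 21 − 1 + 8 = 28 parameters, more than the 23 events.

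Simulated fits with uninformative covariates and a true odds ratio of 4.57 gave a median estimate of about 5.9–6.1 with 21 parameters at 232 patients and 5.4 at 290, against 4.7 with arm and LOC alone.

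**The case against.** The strongest reply is that the primary test contains no error. Planning and analysis use the same test, its error stays below 2.5%, and its power exceeds 80%: about 89–91% uncorrected in the table, and about 84% with a continuity correction (83.7% for the second row). This stands. A reader might infer that the trial is underpowered, or that it wastes power already paid for. The documents do not support either reading, because N was never reduced on account of stratification.

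It is also fair that the gain depends on a LOC mix the protocol does not give, that it shrinks towards nothing as the LOC gradient flattens, and that a LOC-adjusted analysis is already prespecified as supportive. These points limit the size of the concern but do not give a reason to prefer the pooled test.

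On the additional model, three replies stand:

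- It is supportive. No stopping rule and no primary claim rests on it.
- Inflation is milder when there are more events. At 290 patients with 16% versus 8% (assumed, about 35 events) the median odds ratio was 2.44 against a true 2.19.
- The share of fits that fail depends on invented covariate distributions. It ran from 2.4% to 13% at 232 patients with 21 parameters, and was about 70–75% with surgery type split into seven categories. No single failure rate should be quoted.

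A reader might also infer that glove change happens after allocation. The protocol places it during the operation (Visit 2), ahead of wound closure {11d} and before skin closure {20b}; none of these puts it after randomisation. Operation duration is different: Visit 2 runs it to complete skin closure, which follows allocation, and the surgical team is not blinded {17a}. Most of the duration nevertheless precedes allocation.

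**Conclusion.** The concern holds as an available improvement to the primary analysis, with a secondary defect in a supportive model. The pooled primary test is valid and meets its planned power. It is conservative, and a LOC-stratified test would recover about 0.4–2.3 power points at the planning rates, more if the effect is smaller. Direction and mechanism follow from the stratified allocation and Table 2; the size rests on assumed LOC mixes and a common odds ratio across LOC.

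The additional model, as the text fixes it, has about 1.1–1.4 events per parameter. Its odds ratio will tend to overstate the effect, and may not be estimable if type of surgery enters as many categories. This does not touch the primary inference.

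**What to change.** **Primary test.** Replace the pooled test with a Cochran-Mantel-Haenszel z statistic stratified by LOC at both looks, with the same efficacy and futility bounds. Report the Mantel-Haenszel risk difference with its confidence interval. Keep the pooled two-proportion test as a sensitivity analysis. N need not change.

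**Additional model.** Limit it to arm, LOC and two or three named pre-randomisation covariates, or keep the baseline covariates and use Firth penalisation. Leave out total duration to skin closure, and leave out glove change unless it is recorded as done before randomisation.

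**Cost.** LOC is already collected, so no new data are needed. Recruitment began in September 2022 and non-administrative amendments need ethics approval {25}, so this is a protocol amendment plus analysis code. It should be in place before the unblinded interim look, so that neither the change of test nor the cut in covariates can be driven by results. The exploratory model loses some covariates.

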### Outcomes {12}

The primary efficacy endpoint of the study is occurrence of SSI within 30 days postoperatively, according to the internationally accepted and recommended SSI definition by the CDC (Table 1) [6]. This endpoint has been used in previous studies and assures comparability of the results [8–10, 25]. This endpoint is further considered to be of clinical relevance as SSI increases morbidity and mortality of individual patients, direct and indirect costs and prolongs hospital stay as outlined before. The duration of hospital stay is considered as a secondary outcome, in order to evaluate the potential economic benefit of the intervention. In addition, the following outcome measures have been defined as secondary endpoint measures and will be determined by the unit given in parentheses:Rate of SSI by CDC class I–III (superficial, deep, organ-space) (%)Duration of hospital stay up to 30 days after surgery (days);30 days mortality (%);30 days rate of reoperation/relaparotomy (%);30 days rate of postoperative complications in both groups (%). All AE/SAEs will be additionally classified according to the Clavien-Dindo classification of surgical complications and the Comprehensive Complication Index [26, 27].

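### Every death before day 30 is scored as an SSI, so the primary test compares SSI-or-death, while the endpoint is named and the trial is powered for SSI alone

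*Protocol article*

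**What the plan says.** - **Endpoint.** Outcomes {12}: "The primary efficacy endpoint of the study is occurrence of SSI within 30 days postoperatively", by the CDC criteria in Table 1. None of those criteria refers to death. The secondary endpoints listed in the same section include "Rate of SSI by CDC class I–III (superficial, deep, organ-space") and, separately, "30 days mortality".
- **Power.** Sample size {14}: "Assuming SSI rates of 4% and 16% for the experimental and the standard group respectively". On that basis 232 patients, 116 per arm, give "overall 80% power to show superiority of the experimental over the standard arm". Enrolment is raised to 290 (145 per arm) for 20% dropout.
- **Analysis rule.** Statistical methods {20a} says that SSI incidence is compared, and then: "Patients who die before day 30 will be considered as having SSI at time of death regardless of the intervention group". The only qualification concerns patients whose SSI was already recorded before death. They are events in any case, so it affects the date and not the count.
- **Other analyses.** The named sensitivity analysis uses the per-protocol set. The supportive logistic models in section {20b} keep SSI as the dependent variable. Neither is described as dropping the death rule.

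**The concern.** Three parts of the plan describe two different quantities. The endpoint definition and the sample size refer to SSI. The analysis rule produces SSI or death from any cause. Two things follow.

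1. **Interpretation.** The result would be reported as an SSI rate although part of it is mortality. The assumed experimental rate is low: 0.04 × 116 = 4.6 expected SSIs. Two or three unrelated deaths would visibly change that arm's rate, and a chance imbalance in deaths would read as an effect on infection.
2. **Power.** Deaths without SSI that occur equally in both arms raise both event rates and slightly narrow the difference. The same sample then has less power than was calculated for SSI alone.

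The plan itself expects some deaths: section {20a} names death as a reason for not reaching the endpoint, and emergency and LOC IV surgery are eligible.

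**Working it through.** **Inputs from Sample size {14}:** rates 16% and 4%; one-sided alpha 2.5%; power 80%; one interim look at half the information; efficacy bounds 2.963 and 1.969; non-binding interim futility bound 0.555; continuity correction; 116 per arm evaluable, 145 per arm enrolled.

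**Assumption (not in the document):** a proportion m of patients without SSI die before day 30, equal in both arms. The range shown is m = 1% to 5%.

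**Step 1. Reproduce the stated sample size.**
- Fixed design, unpooled variance: (1.960 + 0.842)² × (0.16×0.84 + 0.04×0.96) / 0.12² = 94.19 per arm.
- Group-sequential inflation for these bounds, 1.0556: 94.19 × 1.0556 = 99.42.
- Continuity correction, n/4 × (1 + √(1 + 4/(n×0.12)))² with n = 99.42: 115.49, so 116 per arm and 232 in total.
- Dropout: 232 / 0.80 = 290.

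Both stated totals match exactly using SSI-only rates. The calculation contains no allowance for deaths.

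**Step 2. Rates under the death rule.** Each arm's rate becomes SSI + m × (1 − SSI): control 0.16 + 0.84m, experimental 0.04 + 0.96m. At m = 2% these are 0.1768 and 0.0592.

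**Step 3. Share of events that are deaths without SSI.** At m = 2%: experimental 0.0192 / 0.0592 = 32%; control 0.0168 / 0.1768 = 9.5%.

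**Step 4. Power.** The two-look design was simulated with the stated bounds, an unpooled z with continuity correction, and stopping at the futility bound.

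| m | Control vs experimental | Deaths among events, control / experimental | Power, 116 per arm | Power, 145 per arm |
|---|---|---|---|---|
| 0% | 16.0% vs 4.0% | 0% / 0% | 81% | 90% |
| 1% | 16.8% vs 5.0% | 5% / 19% | 77% | 87% |
| 2% | 17.7% vs 5.9% | 10% / 32% | 72% | 83% |
| 3% | 18.5% vs 6.9% | 14% / 42% | 68% | 79% |
| 5% | 20.2% vs 8.8% | 21% / 55% | 61% | 72% |

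An analytic calculation by the method of Step 1 agrees to within about one percentage point: 80%, 76%, 72%, 68% and 61% at 116 per arm.

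**Step 5. Sensitivity to method.** If the futility bound is not acted on, corrected power at 116 per arm is 79% at m = 1% and 75% at m = 2%. Without the continuity correction it is about 84% and 81% (futility bound applied), from a base of 88%.

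**The case against.** The strongest defence is that the rule is openly pre-specified, identical in both arms, and sensible in itself: without it, a patient who dies early would count as infection-free. That stands. A composite is a legitimate way to handle death, and nothing here shows bias in one direction.

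A reader might infer that the rule necessarily takes power below 80%. The document does not support that, for four reasons.

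- The trial enrols 145 per arm. Under the rule deaths are observed events, and other missing outcomes are multiply imputed, so deaths need not use up the dropout reserve. With all 145 analysed, corrected power stays above 80% at 1% and 2% mortality. This is an upper limit, since imputed outcomes carry less information and some patients will be excluded.
- The sample-size calculation is continuity corrected, but the plan does not say that the test will be. Uncorrected power remains above 80% up to 2% even at 116 per arm.
- The interim look is meant to check the assumed rates and adjust the sample size. If the interim data carry the same coding, added deaths would show up there.
- The mortality range is an assumption. The exclusions (ASA above 3, dialysis, severe immunosuppression, Child-Pugh B/C cirrhosis, revision surgery) may keep it low, and an intervention that also reduced mortality would soften or reverse the loss.

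Two further inferences also fail. Reporting 30-day mortality separately is not double counting; it lets readers see an imbalance in deaths. Nothing requires the class I–III rates to sum to the primary rate, although an imputed event has no CDC class, so a clarifying sentence is useful. An analysis without the death rule could also sit in a statistical analysis plan that is not shown, so its absence here is not counted as a fault.

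None of this makes the tested quantity SSI alone, or makes the three sections agree.

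**Conclusion.** The point holds as a mismatch between endpoint name, power basis and analysis rule. The primary test compares SSI-or-death; the endpoint definition and the power statement refer to SSI. This follows from the printed text and needs no assumption.

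The size of the consequence does rest on assumptions: mortality without SSI equal in both arms, in the range 1% to 5%. Corrected power then lies between 77% and 61% at 116 evaluable per arm, and between 87% and 72% if all 145 are analysed, before any sample-size adjustment at the interim. A flat claim that power falls below 80% would go too far. The effect on interpretation is firmer: because the assumed experimental rate is only 4%, even 2% mortality without SSI would make about a third of that arm's events deaths rather than infections. The change should be made, because it determines what the trial can say about SSI.

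**What to change.** Keep the death rule and make the rest of the plan match it:

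1. Name the primary endpoint *SSI or death within 30 days* in Outcomes {12} and Statistical methods {20a}.
2. Restate the power in Sample size {14} for that composite, over a stated range of mortality without SSI.
3. Pre-specify a sensitivity analysis of the primary comparison using documented SSI only.
4. State that class I–III rates are computed from documented SSIs.

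Making documented SSI the primary variable instead is possible but debatable, because early deaths would then count as infection-free. It is better placed as the sensitivity analysis.

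The cost is wording, a restated power calculation and one extra analysis run. No new data are needed. The downside is that the stated power may look less favourable.
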